### Interim analyses {21b}

No additional interim analyses will be conducted.

### Methods for additional analyses (e.g., subgroup analyses) {20b}

In case of baseline differences between the 2 groups (tACS + MIRT and sham-tACS + MIRT), statistical analyses will be adjusted to take into account specific variables that may have influenced the results for subgroup analysis (e.g., LEDD, illness duration, and age). The post hoc analyses will also be performed with Bonferroni corrected *t*-tests to examine the improvements in all outcome variables through comparisons across different assessment time points. Additionally, distinct exploratory analyses will be conducted for EEG and functional MRI data in order to gain a more comprehensive understanding of the impact of tACS intervention on brain plasticity.

### Methods in analysis to handle protocol non-adherence and any statistical methods to handle missing data {20c}

The intention-to-treat (ITT) analysis will be the primary analysis of this study, with per-protocol (PP) analysis as a secondary analysis in case patients were unable to receive the intervention due to issues related to the intervention itself, such as adverse effects, difficult administration, or adherence problems. Missing data will be handled using the last observation carried forward (LOCF) method. Sensitivity analyses will be conducted if there are imbalanced losses to follow up or excessive attrition.

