### Trial design {8}

The study will be a double-blind, randomized, placebo-controlled trial. The present protocol follows the Standard Protocol Items Recommendations for Interventional Trials (SPIRIT) guidelines and fulfills the SPIRIT checklist [44]. Our hypothesis is that tACS combined with MIRT is superior in terms of efficiency and effectiveness compared to MIRT alone for treating PD. Each patient’s participation in the study will last for 26 weeks, including baseline evaluation (T0), a 10-day intervention period, and assessments at the end of intervention (T1), as well as 4 weeks (T2), 12 weeks (T3), and 24 weeks (T4) post-intervention. Please refer to Fig. 1 for details regarding patient visits and follow-up schedule. Additionally, Fig. 2 provides an overview of all interventions and outcome measures in accordance with SPIRIT 2013 guidelines [45] (Additional file 1).

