### Intervention description {11a}

After the initial baseline assessment (days 1–2), patients will be administered tACS + MITR or sham-tACS + MIRT for a consecutive period of 10 days (days 3–12).

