### Outcomes {12}

#### Primary outcome measures

The primary outcome indicator will be the PDQ-39, which assesses changes in quality of life from T0 to T2, T3, and T4. The PDQ-39 consists of 39 items that are categorized into eight domains: mobility, activities of daily living, emotional, well-being, stigma, social support, cognitions, communication, and bodily discomfort [46]. Patients were instructed to indicate the frequency of occurrence for each corresponding event within the preceding month. The final outcome of the scale encompasses a comprehensive index score, eight sub-core scores, and a weighted percentage reflecting problem severity. Higher scores (ranging from 0 to 100) indicate a greater burden on quality of life (QOL), with − 4.72 and + 4.22 serving as clinically significant thresholds for detecting improvements or deteriorations in QOL among individuals with PD [47]. The PDQ-39 has been translated and validated in multiple languages and cultural settings, making it a recommended tool by the Movement Disorders Society due to its proven effectiveness and stability [48].

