## Data collection and management

### Plans for assessment and collection of outcomes {18a}

The following data will be collected at baseline: gender, age, occupation, educational level, current medication status, and detailed physical and neurological examinations. Inclusion and exclusion criteria will be evaluated. PDQ-39 assessments will be conducted at T0, T2, T3, and T4. MDS-UPDRS III [49, 55], Mini-BES test [50, 56], 6MWT [51, 57], NMSS [52, 58], MoCA [53, 59], and HAMD, as well as other motor symptom scales and non-motor symptom scales, will be assessed at T0, T1, T2, T3, and T4 respectively. MRI and EEG scans will be evaluated at T0 and T1. Levodopa equivalent daily dose (LEDD) data will be collected at T0, T1, T2, T3, and T4. All these assessments will be conducted in a double-blind manner by raters who were unaware of the treatment administered to the patients. At T0 and T1, various safety indicators including blood routine, urine routine, stool routine, liver and kidney function tests, electrocardiogram readings, and other relevant parameters will be evaluated. Any adverse events occurring during the study will be documented. Participants will be asked for their consent regarding the use of their data if they choose to withdraw from the trial. Additionally, participants must obtain permission from the research team to share their pertinent information with university personnel involved in the study or relevant regulatory authorities. Prior to commencing the study, investigators will undergo standardized training on data collection strategies as well as guidelines for utilizing different scales to assess outcomes. Throughout the trial period, professionally trained researchers will collect data to ensure impartiality. In case subjects experience an “on–off” phenomenon during treatment response fluctuations; separate data collection sessions will take place during both “on” and “off” periods for subsequent comparison.

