## Statistical methods

### Statistical methods for primary and secondary outcomes {20a}

SPSS v27.0 software (SPSS Inc., Chicago, IL, USA) will be used for data processing and analysis. Demographic and baseline characteristics of the two groups will be described and analyzed to assess comparability. The PDQ-39 will serve as the primary outcome measure, and an analysis of covariance (ANOVA) model will be employed to estimate the adjusted means of patients’ quality-of-life scores (LSmeans), accounting for baseline differences, as well as calculate 95% confidence intervals for the difference in adjusted means. The count data in the secondary outcome indicators are described by frequency counts. The measurement data are tested for normality using the Shapiro–Wilk method and expressed as mean ± standard deviation if they follow a normal distribution. For non-normally distributed data, they will be described using (P25, P75). Between-group comparisons of motor function, non-motor function-related scale scores, and other secondary indicators between the two groups will be analyzed using appropriate methods based on the type of indicator. Component comparisons such as quantitative information will be analyzed using analysis of variance or Wilcoxon rank sum test. Categorical data will be analyzed by chi-square test or exact probability method, while hierarchical information will be assessed through rank sum Wilcoxon test or CMH test. The significance level for each test will be set at *P* < 0.05.

The MRI pre-processing will be conducted using the data processing assistant for Rs-fMRI, which operates in conjunction with the statistical parametric mapping software (SPM82). Subsequently, the EEG data will undergo offline processing through MATLAB software scripts and the EEGLAB toolbox.

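### LOCF is fixed as the missing-data method for the primary ITT analysis and can bias the PDQ-39 comparisons at T2, T3 and T4, in a direction not known in advance

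*Protocol article*

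**What the plan says.** Section {20c} of the Protocol article sets the population and the missing-data rule together: "The intention-to-treat (ITT) analysis will be the primary analysis of this study", and "Missing data will be handled using the last observation carried forward (LOCF) method". The rule is not limited to particular outcomes or visits, and no other method is named. The only safeguard is conditional: "Sensitivity analyses will be conducted if there are imbalanced losses to follow up or excessive attrition".

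The primary outcome section reads: "The primary outcome indicator will be the PDQ-39, which assesses changes in quality of life from T0 to T2, T3, and T4". Section {18a} confirms the schedule: "PDQ-39 assessments will be conducted at T0, T2, T3, and T4". The end-of-intervention visit T1 is thus absent for the primary outcome. Section {8} places the later visits at 4, 12 and 24 weeks after the intervention, and {11a} gives both arms the same ten-day rehabilitation programme. Section {20a} compares the arms by baseline-adjusted means from an analysis of covariance.

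**The concern.** LOCF assumes that a patient's score stays where it was when last seen. Nothing in the article supports this for a short intensive rehabilitation block in a neurodegenerative disease, followed for 24 weeks.

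The schedule makes the assumption bite in two ways. A patient lost between baseline and T2 has only the baseline score to carry, so the change is set to exactly zero at T2, T3 and T4. A patient lost later has a 4-week score standing in for weeks 12 and 24, or a 12-week score standing in for week 24. The covariance analysis then treats these values as measurements, so its standard errors ignore that they were filled in.

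The long-term effect is an aim of the trial, and T3 and T4 belong to the primary outcome. LOCF puts earlier scores at those visits. It can dilute a real effect, extend one that has faded, or produce one where there is none.

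**Working it through.** **Inputs from the Protocol article.** 27 evaluable patients per group, 10% attrition, 30 randomised per group ({14}). PDQ-39 at T0, T2, T3 and T4 ({18a}). A change of −4.72 as the threshold for improvement (primary outcome measures). The article does not name 4.72 as the design effect; it is used here only as a yardstick.

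**Plan's own figure.** 27 / (1 − 0.10) = 30 per group, which reproduces. About 3 patients per arm would be imputed. The 27 cannot be rebuilt, because no effect size or SD is given.

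**Assumptions, not in the article.** Sham-arm mean changes of −8, −5 and −2 at T2, T3 and T4, so the rehabilitation benefit shared by both arms wanes by 6 points from T2 to T4. Dropouts follow the mean course of their arm. Negative differences favour tACS.

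**Formula.** Bias at a visit = p(active) × (carried mean − true mean, active) − p(sham) × (carried mean − true mean, sham), where p is the proportion lost.

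- **(a) Constant effect of −4.72, 10% of each arm lost before T2.** Carried change is 0, so the estimate is 0.90 × (−4.72) = −4.25 at T2, T3 and T4.
- **(b) Effect of −4.72 at T2 fading to 0 at T4, 10% of each arm lost after T2.** The shared waning cancels. Bias at T4 = 0.10 × (−4.72) = −0.47, a false benefit.
- **(c) No effect at any visit, 20% of active and none of sham lost after T2.** T3: 0.20 × (−8 + 5) = −0.6. T4: 0.20 × (−8 + 2) = −1.2. Reversing the arms gives +1.2 at T4.
- **(d) Fading effect with the dropout in (c).** Active mean is −12.72 at T2 and −2 at T4: 0.20 × (−12.72 + 2) = −2.1.
- **(e) No effect, late dropout of 20% active v 5% sham, shared waning of 4 to 8 points.** 0.15 × 4 = 0.6 and 0.15 × 8 = 1.2 points of spurious T4 benefit. Against 4.72 that is 13% to 25%.
- **(f) No effect and equal dropout, or a constant effect with equal losses only after T2.** The terms cancel and the bias is 0.

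**Simulation at T4.** Covariance analysis, 30 per arm, 3,000 runs, dropout at random. Assumed change SD is 5.3, which −4.72 and n = 27 imply at 90% power and α = 0.05, with between-visit correlation 0.6.

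| Case | LOCF estimate | LOCF rejection rate | Observed data only: rejection rate |
|---|---|---|---|
| (a) | −4.25 | 0.87 (power) | 0.89 (power) |
| (b) | −0.46 | 0.06 | 0.04 |
| (c) | −1.18 | 0.13 | 0.05 |
| (c) with 15% v 5% | −0.59 | 0.07 | 0.05 |
| (d) | −2.10 | 0.25 | 0.05 |

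In the rows with no true T4 difference (all but (a)), the rejection rate is the type I error, and the observed-data analysis was unbiased to within simulation error.

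**The case against.** The best defence is about size. Planned attrition is 10%, follow-up may be done online ({10}), and reminders and a hotline are planned ({18b}). With equal 10% loss the bias is half a point or less. Case (a) is conservative and costs about 2 percentage points of power. The larger figures need marked imbalance: in case (e), 6 patients against 1 or 2 of 30. That is the situation in which {20c} promises sensitivity analyses. This stands as a limit on magnitude.

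It does not rescue LOCF as the primary method. If the sensitivity analyses are triggered, LOCF still gives the primary result. In cases (a) and (b) dropout is equal and at the planned rate, so the imbalance condition would not be met, yet the estimate is off.

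A reader might also object that the article gives no trigger value and no method for the sensitivity analyses. A condensed article may leave those details to the full protocol or analysis plan, so they are not held against it. What can be criticised is that the analyses are conditional.

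**Conclusion.** The article fixes a missing-data method that suits its design poorly, and it should be changed. The bias can affect T2 as well as T3 and T4, because a baseline score carried forward enters all three.

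At equal 10% attrition the size is small: 4.72 becomes about 4.25, or a false benefit of about 0.5 point appears at T4. Spurious T4 benefit of 0.6 to 1.2 points rests on assumed 20% v 5% late dropout and 4 to 8 points of waning of the shared rehabilitation benefit. Type I error of 0.13 to 0.25 arose only with 20% loss confined to the active arm.

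A reader might infer that LOCF must bias the result, or must favour tACS. The documents do not support either: case (f) gives no bias, and reversing the imbalance reverses the sign. The trajectories, dropout splits, SD and correlation are all assumptions. Severity: should-fix.

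**What to change.** Amend {20a} and {20c} before unblinding. Replace LOCF as the primary approach with one of the following:

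- a mixed model for repeated measures on PDQ-39 with arm, visit, arm × visit, baseline and baseline × visit, unstructured covariance, and arm contrasts at T2, T3 and T4; or
- multiple imputation followed by the planned baseline-adjusted analysis of covariance at each visit.

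State that all randomised patients are included. A mixed model confined to those with a post-baseline score would drop everyone lost before T2, which conflicts with an ITT primary analysis. Keep them in by multiple imputation, or by a constrained longitudinal model that treats baseline as an outcome.

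Run a missing-not-at-random sensitivity analysis, delta-adjusted or reference-based, regardless of attrition. Keep LOCF at most as a supportive analysis.

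The cost is revised wording, the ethics committee approval that {25} requires for amendments, and a little more programming. No extra data, visits or patients are needed.

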### Plans to give access to the full protocol, participant-level data, and statistical code {31c}

Participant data is sensitive data and will be provided without participant identification upon reasonable request.

## Oversight and monitoring

### Composition of the coordinating center and trial steering committee {5d}

We have established an independent data and safety monitoring board (DSMB) for this study, which is not sponsored by any particular organization. The committee comprises a rehabilitation specialist, a neurologist, and a statistician who will monitor adherence to the trial design and standard guidelines.

### Composition of the data monitoring committee, its role and reporting structure {21a}

The trial design and adherence to standard guidelines will be overseen by the DSMB. This study, conducted at Beijing Rehabilitation Hospital, is a single-center investigation managed by the DSMB. A committee of rehabilitation specialists will be responsible for controlling the study protocol, while a neurologist will evaluate, manage, and classify all adverse events (AEs) that occur. Additionally, a statistician will review the data for safety purposes. It is important to note that DSMB members are independent of each other with no conflicts of interest.

### Adverse event reporting and harms {22}

The tACS procedure is considered safe, with no apparent short- or long-term harm observed. Potential low-grade adverse events may include seizures, headaches, site irritation pain, etc. However, post-treatment monitoring will be conducted using a safety questionnaire to assess any side effects.

All serious adverse events (SAEs) must be promptly reported within 24 h of occurrence to the principal investigator, ethics committee, and DSMB. Following thorough discussion and evaluation of these issues by the DSMB and principal investigators, they will have discretionary authority to determine whether discontinuation of the trial is necessary.

### Frequency and plans for auditing trial conduct {23}

The DSMB will convene regularly to conduct ongoing reviews of the trial’s progress, both at scheduled intervals every 3 months and throughout the duration of the trial. The DSMB is responsible for ensuring the timeliness, completeness, and accuracy of trial data, thereby necessitating investigators to promptly address any deficiencies or inaccuracies in their reporting. Additionally, a coordinating center will assume responsibility for managing day-to-day operations and providing comprehensive organizational support.

### Plans for communicating important protocol amendments to relevant parties (e.g., trial participants, ethical committees) {25}

Any modifications to the trial protocol must be communicated to and approved by the Ethics Committee of Beijing Rehabilitation Hospital before being implemented. In cases where important protocol modifications may affect the study’s conduct, they will also be reported to the trial registries.

### Dissemination plans {31a}

The results of this study will be published in peer-reviewed journals related to neuroscience and neurorehabilitation. The report will also be presented at national and international conferences and clinical forums and to other relevant health professionals and stakeholders, as well as to the participants. In addition, the included participants will receive a lay summary of their assessment reports after they finished the trial. A final report will be submitted to the trial register.

## Discussion

The aim of this study is to use tACS as an intervention tool for addressing abnormal oscillatory activity in PWP and enhancing overall function and quality of life by modulating neuroplasticity in ganglion-related brain regions. The presence of neural oscillations is linked to different behavioral states observed in PWP [67]. Deviation from physiological frequency bands serves as a distinctive feature of a broad range of pathologies known as thalamo-cortical dysrhythmias or oscillopathies [68]. Dopamine depletion leads to excessive synchronization of beta oscillations (15–30 Hz) in the basal ganglia and its related circuits [69]. Several studies have demonstrated the presence of finely-tuned, narrow-frequency gamma activity (referred to as fine-tuned gamma or FTG activity) in the spectra of local field potentials (LFPs) recorded from the globus pallidus interna (GPi), subthalamic nucleus (STN), and thalamus during rest conditions [70–72]. This activity exhibits contralateral enhancement during voluntary movements, thus exhibiting an opposite direction to beta-band activity. The use of tACS has shown its ability to induce neuroplasticity and regulate cortical function [22, 73].

TACS can effectively ameliorate motor retardation in PWP by regulating abnormal oscillations within the basal ganglia-thalamo-cortical network at the level of the primary motor cortex [27]. Gamma-tACS plays a crucial role in preparing and executing movements, and the improved motor function induced by gamma-tACS is associated with alterations in blood-oxygen-level dependent (BOLD) activity in M1. Furthermore, the effects of tACS extend beyond alterations in neural activity solely within the targeted region, encompassing functional connectivity and compensatory modulation occurring within task-related brain networks [74].

There is ongoing debate regarding the impact of weak currents applied to the scalp on neural activity, as studies have shown that scalp currents are attenuated by approximately 75% due to soft tissues and the skull. Low-intensity current stimulation is typically employed for localized and superficial dermal stimulation [75–78]. Conversely, higher-intensity AC stimulation exhibits a more pronounced effect in entraining neural oscillations and influencing neural circuits. Notably, one study demonstrated a convincing induction effect on brain networks through strong AC stimulation administered to anesthetized patients via intracranial screw electrodes [79]. Measurements conducted on rodents and human cadaver brains have revealed that scalp-applied stimulation necessitates a minimum current exceeding 6 mA to transiently and efficiently alter brain networks; however, Hi-tACS remains underutilized in PWP [77]. However, a tACS study utilizing a frequency of 77.5 Hz did not yield significant improvements in motor and psychological symptoms among PWP when compared to a placebo intervention [80]. We have identified several potential reasons for these findings. Firstly, the previous trial only administered tACS treatments 10 times per patient, which may have resulted in an insufficient cumulative dosage that contributed to the ultimately negative outcome. In our experiment, each patient received 2 daily sessions of tACS over a period of 10 days, totaling 20 treatment sessions, thereby increasing the dosage in order to achieve more favorable results. Additionally, the prior investigation had a limited sample size of only 23 participants for their simple tACS study, potentially influencing the negative outcomes observed. To address this limitation and provide stronger data support for our trial, we aimed to recruit 60 participants and expand the sample size accordingly.

The previous trials have primarily focused on the administration of tACS alone, whereas our trial integrates tACS with MIRT based on a “central-peripheral-central” model. In this novel rehabilitation model, positive feedback is utilized to enhance brain plasticity and the rehabilitative effects following brain injury. MIRT is a goal-directed rehabilitation program designed to address functional impairments caused by Parkinson’s disease through explicit and implicit learning strategies [40]. Randomized controlled studies have demonstrated that MIRT significantly improves the quality of life in PWP [81]. Finally, the previous study solely compared behavioral outcomes pre- and post-treatment of subjects. We have previously conducted a study on 4 Hz tACS in PD using cortico-subcortical co-activation pattern (CAP) analysis on rs-fMRI data, which demonstrated that cortical and subcortical regions exhibit co-activation during the resting state and form distinct CAPs. Moreover, the occurrence of cortical and subcortical CAPs can be enhanced following tACS treatment [82]. This alteration in brain function may precede the observed behavioral changes. Therefore, we have also incorporated EEG and fMRI examinations to assess brain network function in this study.

Through a randomized double-blind design, this trial will validate the efficacy and long-term effects of tACS on quality of life and overall functioning among PWP who receive true tACS or sham tACS. The ultimate goal is to establish a correlation between the behavioral improvements induced by tACS in PWP and changes in the functional connectivity of neural networks, as well as biomarkers of neurobiological plasticity using structural and functional magnetic resonance imaging techniques. Additionally, we aim to investigate the interaction between the stimulated area’s functional connectivity and other brain regions within the executive function system. This study also seeks to examine the relationship between baseline neural circuits in the brain and those after tACS intervention, particularly focusing on any effects on emotional and motor circuits. By applying a novel rehabilitation program combining tACS with MIRT for PWP, our results can contribute towards establishing a standardized model for PD rehabilitation that will provide evidence-based medical support for enhancing rehabilitation treatment models and improving the quality of life for PWP.

